## Abstract

**Introduction:**

Early detection of cardiovascular disease in primary care is a public health priority, for which the clinical and cost-effectiveness of an artificial intelligence-enabled stethoscope that detects left ventricular systolic dysfunction, atrial fibrillation and cardiac murmurs is unproven but potentially transformative.

**Methods and analysis:**

TRICORDER is a pragmatic, two-arm, multi-centre (decentralised), cluster-randomised controlled trial and implementation study. Up to 200 primary care practices in urban North West London and rural North Wales, UK, will be randomised to usual care or to have artificial intelligence-enabled stethoscopes available for use. Primary care clinicians will use the artificial intelligence-enabled stethoscopes at their own discretion, without patient-level inclusion or exclusion criteria. They will be supported to do so by a clinical guideline developed and approved by the regional health system executive board. Patient and outcome data will be captured from pooled primary and secondary care records, supplemented by qualitative and quantitative clinician surveys. The coprimary endpoints are (i) difference in the coded incidence (detection) of heart failure and (ii) difference in the ratio of coded incidence of heart failure via hospital admission versus community-based diagnostic pathways. Secondary endpoints include difference in the incidence of atrial fibrillation and valvular heart disease, cost-consequence differential, and prescription of guideline-directed medical therapy.

**Ethics and dissemination:**

This trial has ethical approval from the UK Health Research Authority (23/LO/0051). Findings from this trial will be disseminated through publication of peer-reviewed manuscripts, presentations at scientific meetings and conferences with local and national stakeholders.

**Trial registration number:**

NCT05987670

STRENGTHS AND LIMITATIONS OF THIS STUDYUse of real-world data for outcomes evaluation minimises the administrative impact on frontline primary care services and enhances the generalisability of results.Integration of artificial intelligence predictions with routinely collected electronic medical record data allows sensitivity analyses at the level of patient, site and region.Outcome assessment from routine medical coding lacks the granularity and fidelity of primary research form collection.

## Introduction

 Early detection of cardiovascular disease is a global public health priority.^1^,^3^ Heart failure (HF), atrial fibrillation (AF) and valvular heart disease (VHD) can have common pathophysiology and significant mortality and morbidity.^4^,^7^ Given the reported adult prevalence of HF of 2%, the recognised incidence of HF in Europe of 5 per 1000 person-years in adults^8 9^is likely to be an underestimate.^10^,^13^ HF is deadlier than common, serious cancers,^14^ profoundly impacting quality of life and costing the UK National Health Service (NHS) over £2 billion per year —or over 2% of its annual budget.^15 16^ Unacceptably, 70%–80% of all new HF diagnoses are only made after an emergency hospital admission, despite most patients having been seen in primary care with opportunities for detection and therefore earlier initiation of disease-modifying treatment, ^17 18^expected to translate to improved survival, quality of life and health service utilisation costs.^18^

Notwithstanding the mixed evidence of the the effectiveness of screening programmes to improve mortality and stroke associated with AF, the substantial clinical and health economic costs of AF and VHD are similarly driven by late diagnosis.^19 20^

Across these cardiac conditions, early detection reduces the risk of disease progression and improves survival, through the initiation of inexpensive, guideline-directed therapies.^21^,^23^ However, primary care providers face the challenge that symptoms (if present) are frequently non-specific,^24 25^ and there are no universally effective point-of-care screening tools to identify the diagnosis or diagnostic pathways.

We have recently shown that artificial intelligence (AI) applied to ECG and phonocardiogram (PCG) waveforms captured by a ‘smart’ stethoscope can detect left ventricular ejection fraction ≤40%,^26^ the cause of heart failure with reduced ejection fraction (HFrEF, the most common form of HF), AF and cardiac murmurs–a cardinal examination finding in valvular heart disease.^27^ The statistical performance of these three AI algorithms has been shown to be high and consistent against international external validation studies.^28^ This takes a familiar clinical tool with an established workflow and augments examination findings with actionable additional insights, taking only 15 seconds.^26^ The clinical and health economic impact of deploying such a triple point-of-care AI detection tool in primary care practices is unknown. Furthermore, the determinants of successfully implementing^29^,^31^ such an innovation in routine clinical practice are also not known, given the historical failure of AI technology adoption in healthcare systems that is partly attributable to inattention to implementation science and a failure to overcome bias.^32 33^

The objective of the TRICORDER study is therefore to conduct a real-world, decentralised cluster-randomised controlled trial and implementation study to determine if providing primary care teams with an AI stethoscope improves early diagnosis of HFrEF, AF and VHD. Secondary objectives include measurement of cost-effectiveness, examination of implementation strategies and identifying the determinants of uptake and utilisation of the AI stethoscope in routine clinical practice. This report describes the clinical and policy context for this publicly funded clinical trial, details of the protocol and plans for implementation and expected findings with a focus on implications for widespread adoption in health systems.

## Methods and analysis

### Setting

TRICORDER is set within the primary care system of the NHS. General practitioners (GPs) within primary care teams are the gatekeepers to most specialist diagnostic and management services in the NHS through nationally agreed pathways recommended by the National Institute for Health and Care Excellence (NICE, figure 1). Each primary care practice (>8000 in UK) serves an average list of 8500 patients in the community.^34^ Typically, patients in whom the GP suspects HF are referred for natriuretic peptide (NP) testing,^35^ which may be via in-practice phlebotomy or via hospital appointment. The NP level determines the urgency of referral for echocardiography and specialist review. There is substantial geographical variation in access to community-based echocardiography services and lead times to hospital outpatient clinic review.^36^

**Figure 1 F1:**
[figure not shown]
NICE diagnostic pathway for HF. There are substantial delays to confirmatory echocardiographic testing and specialist review for those who are referred for suspected HF through this pathway, such that only 10% of patients complete the pathway to time and target. HF, heart failure; NICE, National Institute for Health and Care Excellence; NT-pro-BNP, N-terminal pro-B-type natriuretic peptide.

### Study design

TRICORDER is an open-label, two-arm cluster-randomised controlled trial. Taking a decentralised approach, primary care practices in the NHS North West London Integrated Care System (NWL ICS, 2.8 million residents, figure 2) and the Betsi Cadwaladr University Health Board (BCUHB, 670 000 residents) in North Wales, UK, will be enrolled for 18 months.

**Figure 2 F2:**
[figure not shown]
Map of London, with the boroughs of North West London stratified by Index of Multiple Deprivation deciles

Each individual primary care practice employing GPs serves as a cluster—the unit of participation and randomisation. Each participating cluster will variously employ GPs, practice nurses, physician associates and other healthcare professionals who constitute the care team. This unit of recruitment was chosen because the NHS' clinical, financial and information governance processes are standardised at this level.

### Sample size

Interrogation of the Discover dataset^37^ (UK Secure Data Environment for TRICORDER endpoint analysis) suggests an incidence rate of HF of 0.62/1000 patients per year. Combining NWL (n=350) and North Wales (n=>50), there are at least 400 potentially eligible study sites. We estimate that each GP practice will have at least 60 eligible patients per year who will receive a stethoscope examination as part of their routine clinical care. Estimating a conservative recruitment ratio of only 50%, we anticipate 200 GP practices being recruited. This provides an eligible study population of 6000 patients per study arm. A review of prior literature in the field indicates an intracluster correlation coefficient of 0.01.^38^

Utilising these estimates and assumptions, we would have over 80% power to detect a statistically and clinically significant mean difference if HF is diagnosed at a rate of 0.79/1000 patients in the intervention group, assuming a two-tailed test with a type I error of 0.05. This corresponds to a relative increase of 22%, which is deemed to be clinically meaningful (~17 to 22 HF diagnoses/GP practice).

The power calculation refers to overall HF, which includes all relevant ICD-10 and SNOMED-CT codes (used in UK primary care), rather than the codes relating to HFrEF specifically. There are three reasons for such an inclusive approach.

First, we aim to mitigate an artificially low incidence of HFrEF due to coding heterogeneity in primary care. Preliminary analysis of the Discover dataset revealed substantial heterogeneity in clinical coding of HF subtypes. This is well recognised in recent studies.^39^

Second, this approach captures the effect on clinician behaviour from participation in the study—it is feasible that more of all HF subtypes may be detected during the study period.

Finally, this approach enables rapid clinical and health economic endpoint analysis, avoiding the time and cost burden of manual data entry/data collection from chart arbitration, which would otherwise risk undermining the scalability of TRICORDER and set an impractical precedent for longer-term outcomes analyses.

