### Inclusion and exclusion criteria

Eligible primary care practices must meet the following inclusion criteria:

Caring for adult patients ≥18 years old.Able to request natriuretic peptide blood testing (a standard screening test for HF in patients with symptoms) and initiating the HF diagnostic pathway recommended by the NICE^35^.

Exclusion criteria:

Poor WiFi and/or mobile data connectivity within primary care consulting rooms, prohibiting the use of the AI-enabled stethoscope.Not providing face-to-face patient consultations.

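### The planning rate of 0.62 HF diagnoses per 1000 patients per year does not fit the article's own counts of 17 to 22 per practice, list size of 8500 or target of 0.79 per 1000.

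*Protocol article*

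**What the plan says.** Protocol article, Sample size: Discover "suggests an incidence rate of HF of 0.62/1000 patients per year". The section calls Discover the environment for endpoint analysis and says that the calculation covers overall HF, with all relevant codes. Power is claimed "if HF is diagnosed at a rate of 0.79/1000 patients in the intervention group", and the section adds: "This corresponds to a relative increase of 22%, which is deemed to be clinically meaningful (~17 to 22 HF diagnoses/GP practice". The base rate is per year. The target and the per-practice counts carry no time unit. The section does not say whether the 1000 patients are the whole list, the adults on it, or the patients examined. The only patient number it uses is that "each GP practice will have at least 60 eligible patients per year who will receive a stethoscope examination".

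Three other places bear on this:

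- Introduction: "Given the reported adult prevalence of HF of 2%, the recognised incidence of HF in Europe of 5 per 1000 person-years in adults", a figure the authors think is likely too low.
- Setting: the average practice list is 8500 patients.
- Study design: practices take part for 18 months. The two regions have 2.8 million and 670 000 residents.

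**The concern.** The base rate sets the scale of the plan: the expected number of events, the target rate, and the size of a given absolute gain relative to usual care. Here the rate, the list size and the counts per practice are all printed, so they can be checked against each other. If the counts are right, the base rate is too low and the target of 0.79 lies below what usual care would produce. If the base rate is right, the counts used to illustrate a clinically meaningful effect are two to three times too high.

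The gap to the Introduction's adult incidence points the same way. Restriction to HFrEF codes cannot explain it, because the planning rate is stated to cover all HF.

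**Working it through.** **Inputs.** Base rate 0.62 per 1000 per year, target 0.79 per 1000 and counts of 17 and 22 per practice (Sample size); average list 8500 (Setting); 18 months, or 1.5 years (Study design); 5 per 1000 adult person-years (Introduction).

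**1. Trying to reproduce the counts of 17 and 22.** Diagnoses per practice = list × rate × years.

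| | Rate per 1000 | 1 year | 1.5 years | Stated |
|---|---|---|---|---|
| Control | 0.62 | 8500 × 0.00062 = 5.3 | 7.9 | 17 |
| Intervention | 0.79 | 8500 × 0.00079 = 6.7 | 10.1 | 22 |

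The counts are not reproduced. The control count is too high by 17/5.27 = 3.2 or 17/7.905 = 2.2. On the 60 examined patients, the rate gives 60 × 0.00062 = 0.04 diagnoses a year.

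**2. Which denominator would reproduce them?** 17/0.00062 = 27,400 and 22/0.00079 = 27,800 patient-years per practice. The two agree, so the counts and rates are similar in ratio (22/17 = 1.29, 0.79/0.62 = 1.27) but differ in scale. An average list over 18 months supplies 8500 × 1.5 = 12,750 patient-years. A list of about 27,400/1.5 = 18,300 would be needed. The regional figures do not suggest one: 2.8 million residents over the 350 sites counted in North West London is 8000 per site, and 670 000 over at least 50 in North Wales is at most 13,400. (Residents are only a proxy for registered patients.)

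**3. Rate implied by 17 per practice.** 17/8500 = 2.0 per 1000. If the 17 accrue over 18 months, the rate is 2.0/1.5 = 1.33 per 1000 per year. Both exceed 0.79.

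**4. Time unit of the target.** If 0.79 were cumulative over 18 months, the matching control value would be 0.62 × 1.5 = 0.93, again above the target. Target and base rate are coherent only if both are annual.

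**5. Comparison with the Introduction.** 5/0.62 = 8.1. Children in the denominator do not close the gap. If adults are 75% to 85% of a list (an assumption; the article gives no figure), an all-age 0.62 becomes 0.62/0.85 = 0.73 to 0.62/0.75 = 0.83 per 1000 adults, still about one-sixth to one-seventh of 5.

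**6. What the base rate does to the effect.** The planned difference is 0.79 − 0.62 = 0.17 per 1000. That is 27% of 0.62, 13% of 1.33 and 8.5% of 2.0. The stated 22% is obtained only against the intervention rate: 0.17/0.79 = 21.5%.

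**The case against.** The best defence is that 0.62 is a local coded rate from the platform that will supply the endpoint for North West London. The endpoint is coded incidence, so such a rate is a sounder planning input than a European epidemiological figure, and the authors acknowledge that routine coding is uneven. This stands. If the analysis uses the same codes, denominator and time unit as the query, the control rate would be near 0.62 and the target would lie above it. The Introduction's figure therefore cannot show that 0.62 is wrong. Dividing its 2% prevalence by 0.62 to get an implausibly long time lived with HF would also mix two sources, and proves nothing about the local data.

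A reader might infer that eligibility defines an adult study population to which the adult incidence applies. It does not. The age item, "Caring for adult patients ≥18 years old", is a condition on practices, and the Intervention arm section sets no criteria for individual patients.

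It is also fair to say that the article attaches clinical meaning to a relative increase, and that a journal article may leave the query specification to the full protocol. But the defence does not reach steps 1 to 3. They use the article's own rate, list size and counts, and these contradict each other wherever the specification is written down.

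**Conclusion.** The concern holds as an internal inconsistency. The base rate, the average list and the per-practice counts cannot all be true of the same population: the counts are 2.2 to 3.2 times what the rate gives, depending on whether they cover 18 months or one year. This assumes that practices in the trial are about average in size and that the counts refer to the whole list.

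Two stronger readings are tempting and unsupported. The first is that the control arm will in fact exceed 0.79 per 1000. That follows if the counts are right, but the article does not show whether the counts or the rate is in error. The second is that the error would distort a test or a stopping decision. The Statistical analysis section compares the arms by mixed-effects logistic regression. The 12-month futility option under Interim analysis refers to a clinically significant difference without linking it to 0.79 or 0.17 per 1000. The damage is to the planning figures and to the stated size of a worthwhile effect.

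That the stated inputs give roughly 5% power rather than 80% is a separate fault. A corrected base rate would not by itself remove it.

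**What to change.** 1. Re-run the Discover query on the population, code list and person-time that the endpoint will use. Confirm or replace 0.62, and state the denominator. Discover covers North West London, so say what is assumed for North Wales.
2. Keep the clinically meaningful effect as a ratio to the control rate, and derive the target from it with its time unit. For illustration, a ratio of 1.27 (0.79/0.62) gives 0.79 from 0.62, 1.70 from 1.33 and 2.55 from 2.0 per 1000.
3. Recalculate the diagnoses per practice from the same rates, list size and period, and say which period they cover. Add a sentence explaining any remaining gap to the incidence in the Introduction.
4. Restate the power on these inputs.

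The cost is one query on a platform already in use and a rewritten paragraph. No patients or practices are added.

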### Data sources

In the NWL ICS, patient-level complete primary and secondary care clinical and cost data is pseudonymised and pooled within Discover-NOW, a UK Trusted Research Environment.^37^ AI stethoscope usage statistics and AI predictions will be integrated into the Discover-NOW and tagged to appropriate patient records. The study team will access this real-world data platform to measure population-level clinical and health economic outcomes, in addition to patient-level sensitivity analyses for NWL ICS.

At BCUH, only the direct care team will access medical records and record population-level outcomes as part of a service evaluation (coprimary endpoints), using epidemiological methods only.

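### The claimed power of over 80% does not follow from the printed derivation: 6000 patients per arm at 0.62 versus 0.79 per 1000 gives about 4 versus 5 events and about 6% power

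*Protocol article*

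**What the plan says.** All the planning inputs are in the Sample size section of the protocol article.

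- Control rate: the Discover dataset "suggests an incidence rate of HF of 0.62/1000 patients per year".
- Cluster size: "each GP practice will have at least 60 eligible patients per year who will receive a stethoscope examination".
- Population: with 200 practices expected, "This provides an eligible study population of 6000 patients per study arm".
- Clustering: an "intracluster correlation coefficient of 0.01", taken from prior literature. The scale is not stated.
- Conclusion, which the section says it draws from the inputs above: "we would have over 80% power to detect a statistically and clinically significant mean difference if HF is diagnosed at a rate of 0.79/1000". The last figure is the rate in the intervention arm, and the test is two-sided at 0.05.
- Gloss on the effect: a relative increase of 22%, or roughly 17 to 22 HF diagnoses per practice.

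Two other sections bear on the denominator. Under Setting, each UK practice "serves an average list of 8500 patients in the community". Under Data sources, "The study team will access this real-world data platform to measure population-level clinical and health economic outcomes". The Intervention arm section sets no patient-level inclusion or exclusion criteria.

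**The concern.** HF at well under 1 per 1000 per year is a rare outcome. In 6000 people it produces a handful of events, and a difference of about one event between arms cannot be detected with 80% power. The 0.62 per 1000 reads as a rate in a whole registered population, yet it is applied to the small subset expected to be examined with a stethoscope.

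This is the only power justification in the document, and it concerns the first coprimary endpoint. Two readings depend on it. A null result would be interpreted against a stated power of over 80%. The Interim analysis section also lets the steering group stop for futility at 12 months if no clinically significant difference has appeared, and that judgement needs a power figure that can be reproduced.

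**Working it through.** **1. The plan's own calculation.** Inputs from Sample size: p1 = 0.00062, p2 = 0.00079 (read as per year), 60 patients × 100 practices = 6000 per arm, ICC 0.01, two-sided 0.05.

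- Expected events per arm-year: 6000 × 0.00062 = 3.72 and 6000 × 0.00079 = 4.74.
- Formula: z = (p2 − p1) / √{DE × [p1(1 − p1) + p2(1 − p2)] / n}. Power = Φ(z − 1.96) + Φ(−z − 1.96). DE is the design effect, 1 + (m − 1) × ICC.
- No clustering: z = 0.351, power 6.4%.
- DE = 1 + 59 × 0.01 = 1.59: z = 0.278, power 5.9%.
- 18 months taken as 90 patients per practice, 9000 per arm, DE = 1 + 89 × 0.01 = 1.89: power 6.1%.
- Exact enumeration of the chi-square test at 6000 per arm: 5.6%.
- Patients needed per arm for 80% power before clustering: (1.96 + 0.8416)² × [p1(1 − p1) + p2(1 − p2)] / (p2 − p1)² ≈ 383,000.

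The stated figure of over 80% is not reproduced.

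**2. The other figures in the paragraph.**

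- 0.79/0.62 = 1.274, a 27% increase. A figure near 22% appears only when the difference is divided by the intervention rate: 0.17/0.79 = 21.5%.
- 60 patients give 60 × 0.00062 = 0.04 and 60 × 0.00079 = 0.05 diagnoses per practice-year.
- A list of 8500 gives 5.3 and 6.7 per year (7.9 and 10.1 over 18 months).
- To reach 17 and 22 diagnoses at the stated rates takes 17/0.00062 ≈ 27,400 and 22/0.00079 ≈ 27,800 patient-years per practice.

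**3. The registered list as denominator.** Take 100 practices × 8500 = 850,000 per arm, with equal list sizes assumed. The 8500 is the UK average list; it is not specific to adults or to the trial regions.

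*ICC 0.01 on the proportion scale:*

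- DE = 1 + 8499 × 0.01 = 85.99.
- Power is 7.4% over 1 year, and 8.6% over 18 months (risks multiplied by 1.5).
- The implied between-practice coefficient of variation (CV) is k = √[ICC(1 − p1)/p1] ≈ 4.0 at 1 year, or about 3.3 with the 18-month risk.
- 80% power would need an ICC of at most about 0.00014 (1 year) or 0.00027 (18 months).

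*ICC 0.01 on the latent scale of a logistic mixed model*, which is the model named under Statistical analysis:

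- Random-effect variance = 0.01 × (π²/3)/0.99 = 0.033, so k ≈ 0.18.
- Cluster-rate formula: z = (p2 − p1) / √{[(p1 + p2)/y + k²(p1² + p2²)]/100}, where y is person-years per practice.
- y = 8500: z = 3.81, power 97%.
- y = 12,750 (18 months): z = 4.48, power 99%.

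*By assumed CV, same formula, y = 12,750:*

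| k | Power |
|---|---|
| 0.3 | 97% |
| 0.4 | 90% |
| 0.5 | 81% |
| 0.6 | 70% |
| 1.0 | 36% |

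These values of k are assumptions, since the document gives no CV.

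**The case against.** The best defence is that 6000 is a loose description and that the real calculation used registered populations. The endpoint is measured at population level, and with 8500 per practice and the ICC read on the latent scale the power is well above 80%. The reference to a mean difference and to 17 to 22 diagnoses per practice may also point to a comparison of practice means. With 100 practices per arm, 17 versus 22 reaches 80% for a between-practice SD up to 5/(2.80 × √0.02) ≈ 12.6.

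Part of this stands. A reader might infer that no combination of the stated inputs reaches 80%. The document does not support that, because the scale of the ICC is not given and one reading on the list denominator gives 97% to 99%. The 7% to 9% result holds only on the proportion scale, and its implied CV of 3 to 4 is itself a reason to doubt that reading.

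The defence does not rescue the printed statement. The text ties the power to the estimates it has just listed, and these include 6000 per arm. The 17 to 22 figure is incompatible with the stated rates under either denominator. An unseen analysis plan could contain a sound calculation, but it could not make this one follow from its inputs.

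A reader might also suspect a misplaced decimal, since 62 versus 79 per 1000 with 6000 per arm and design effect 1.59 gives about 82%. The document does not say that such rates were used, so this remains a guess.

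**Conclusion.** Wrong as written. At the stated 6000 per arm and the stated rates, power is about 6%, and no choice of standard two-sided test or of a 12- or 18-month period brings it near 80%. The 22% and the 17 to 22 diagnoses per practice are inconsistent with the same rates. This conclusion rests only on printed inputs, with the 0.79 taken as an annual rate like the 0.62.

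A reader might go further and conclude that a trial of 200 practices is underpowered. That is not shown. On registered-list person-years over 18 months, power passes 80% if the between-practice CV is about 0.5 or less and falls below it at 0.6 and above. These figures assume 100 practices per arm with equal lists of 8500. The CV for this outcome is not in the document, so the actual power is unknown.

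**What to change.** In the Sample size section:

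1. Withdraw the statement of over 80% power based on 6000 examined patients per arm.
2. Restate power, or the smallest detectable rate ratio, for 200 practices, with registered-list person-years over the trial period as the denominator.
3. State the scale of the ICC of 0.01, or replace it with a between-practice CV for coded HF incidence estimated from the Discover data already interrogated.
4. Correct the 22% and the 17 to 22 diagnoses per practice so that they match the rates and denominator used.

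The cost is one recalculation and revised wording. The downside is that the restated power may be less favourable than the present claim. Whether the number of practices is adequate can be judged only once the between-practice variation is known.

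### The target effect of 0.62 to 0.79 per 1000 is a 27% relative increase, not 22%, and the per-practice counts are too high for those rates at the stated list size

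*Protocol article*

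**What the plan says.** The Sample size section of the protocol article describes the target effect in three ways.

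- **As rates.** The regional dataset "suggests an incidence rate of HF of 0.62/1000 patients per year", and the power statement applies "if HF is diagnosed at a rate of 0.79/1000 patients in the intervention group". The target rate carries no time unit of its own.
- **As a percentage and as counts.** "This corresponds to a relative increase of 22%, which is deemed to be clinically meaningful (~17 to 22 HF diagnoses/GP practice". The counts have no period and no denominator.
- **As a power claim.** "we would have over 80% power to detect a statistically and clinically significant mean difference", "assuming a two-tailed test with a type I error of 0.05".

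Two other sections bear on the counts. The Setting section says that a UK primary care practice "serves an average list of 8500 patients in the community". The Study design section gives an enrolment period of 18 months and 2.8 million residents for North West London.

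**The concern.** The rates, the percentage and the counts are meant to describe one effect, but a quick division shows that the percentage does not follow from the rates. The counts also look large for a practice of ordinary size at well under one diagnosis per 1000 patients per year.

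This matters because it is the only place where the article puts a number on a clinically meaningful effect for a coprimary endpoint. A reader who takes the percentage at face value will believe that the trial is sized for a 22% increase, when the printed rates describe a larger one. A reader who takes the counts at face value will expect two to three times as many diagnoses per practice as the rates imply.

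**Working it through.** **Inputs.** Control rate 0.62 per 1000 per year, target rate 0.79 per 1000, stated increase 22%, counts 17 and 22 per practice, 60 examined patients per practice per year, and 350 potential sites in North West London (all Sample size). Average list 8500 (Setting). Enrolment 18 months and 2.8 million residents in North West London (Study design). The target rate is read as annual, like the control rate.

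**Step 1: reproduce the 22%.**

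| Definition | Calculation | Result |
|---|---|---|
| Increase on the control rate | 0.79/0.62 - 1 | 27.4% |
| Difference over the midpoint | 0.17/0.705 | 24.1% |
| Log ratio | ln(0.79/0.62) | 0.242 |
| Difference over the intervention rate | 0.17/0.79 | 21.5% |

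Only the last rounds to 22%. The same division applied to the counts gives 5/22 = 22.7%. Neither is an increase over control.

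**Step 2: can rounding of the rates explain it?** The smallest ratio is 0.785/0.625, which gives 25.6%. The largest is 0.795/0.615, which gives 29.3%. The range excludes 22%.

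**Step 3: what would a 22% increase be?** 0.62 x 1.22 = 0.756 per 1000, not 0.79.

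**Step 4: ratio of the counts.** As printed, 22/17 - 1 = 29.4%, but both counts are rounded and marked approximate. Rounding allows 21.5/17.5 - 1 = 22.9% up to 22.5/16.5 - 1 = 36.4%. Starting from 17:

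- A 27.4% increase gives 17 x 0.79/0.62 = 21.7, which rounds to 22.
- A 22% increase gives 17 x 1.22 = 20.7. Even 17.5 x 1.22 = 21.3 does not round to 22.

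So the counts agree with the rates on the ratio, and 22% is the outlier.

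**Step 5: level of the counts.** Expected diagnoses = denominator x rate x years.

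| Denominator per practice | One year | 18 months |
|---|---|---|
| 8500 (stated average list) | 5.3 to 6.7 | 7.9 to 10.1 |
| 8000 (2.8 million/350) | 5.0 to 6.3 | 7.4 to 9.5 |
| 60 examined patients per year | 0.04 to 0.05 | 0.06 to 0.07 |

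None reaches 17 to 22. At a list of 8500, the printed counts exceed the one-year figures by a factor of 3.2 to 3.3 (17/5.27 and 22/6.715) and the 18-month figures by about 2.2 (17/7.9 and 22/10.07).

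**Step 6: what would the counts need?**

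- With the rates as printed: 17/0.00062 = about 27,400 and 22/0.00079 = about 27,800 person-years per practice. That is 3.2 to 3.3 years at a list of 8500, or a list of about 18,300 to 18,600 over 18 months.
- With a list of 8500 and one year: 17/8500 = 2.0 and 22/8500 = 2.6 per 1000, about three times the printed rates.

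**The case against.** The strongest reply is that the target is fixed by the two absolute rates, so the percentage is only a label. Replacing 22% with 27% changes no sample size, allocation or analysis. This stands, and it limits the point to a wrong description of the effect, unless 22% was the intended target. The intention cannot be read from the article. Division by the intervention rate is the likely explanation for 22%, but the calculation is not shown.

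A second reply is that 8500 is a UK average and is not presented as an input to the sample size. That is true, but North West London's own figures give about 8000, and the 60 examined patients per practice give far less than one diagnosis. No denominator in the article yields 17 to 22.

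Four stronger readings are tempting, and the article does not support them.

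- **That the counts contradict the rates in ratio as well as in level.** Step 4 shows that they fit 27% within rounding.
- **That the trial loses a specific amount of power if the true effect is 22%.** Any such figure presumes a design with exactly 80% power at 0.79. The printed inputs do not describe one. With 6000 patients per arm, 60 per practice and an intracluster correlation of 0.01, the design effect is 1 + 59 x 0.01 = 1.59, the effective size is 6000/1.59 = 3774 per arm, and power at these rates is about 5%. That gap is a separate matter and lends no weight to this one.
- **That the error carries into the 12-month futility review.** The Interim analysis section speaks of clinical significance without giving a threshold or referring back to this figure.
- **That the counts must be the wrong element.** The rates could be at fault instead. The Introduction cites 5 per 1000 person-years in European adults, about eight times 0.62 (5/0.62 = 8.1).

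**Conclusion.** The point holds in two parts.

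1. **The relative increase is misstated.** The printed rates give 27.4%, with 25.6% to 29.3% the widest range that rounding allows. This needs no assumption beyond reading both rates on the same time base, which the article's own comparison requires.
2. **The per-practice counts do not follow in level from the rates.** They are about 3.2 to 3.3 times the one-year expectation and about 2.2 times the 18-month expectation at a list of 8500. This rests on 8500 being roughly right for the participating practices, which the North West London figures support. It does not establish whether the counts or the rates are wrong.

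The first part is certain and must be corrected, because it describes the effect that the article calls clinically meaningful. The second is a reconciliation that only the sponsor can complete.

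**What to change.** **Relative increase.** Choose one and state it consistently:

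- keep 0.79 per 1000 as the target and give the increase as 27% (rate ratio 1.27); or
- if 22% is the agreed clinically meaningful effect, set the target at 0.756 per 1000 and restate the power for that rate.

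**Counts.** Give the period and the denominator, check them against the source data together with the rates, and correct whichever is wrong. If the rates stand, the counts are about 5.3 to 6.7 per practice per year at a list of 8500 (7.9 to 10.1 over 18 months). These should not be inserted before the rates are confirmed, since that could entrench a wrong rate. The target rate should also carry its time unit.

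**Cost.** The first option is a change of wording. The second needs one recomputation of power for a smaller effect. Reconciling the counts needs a check of the dataset extract. Correcting the description requires no change to the trial's conduct.
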